### The treatment, follow-up and duration of cases of adverse events/serious adverse events

All adverse events/important adverse events, researchers should take the necessary measures according to their severity, and follow up to solve, returned to baseline level, proved unable to solve/permanent or death.

### The judgment and treatment of parameter abnormalities of laboratory test

Clinical significance of abnormal laboratory data of all researchers must obtain the trial period to evaluate. Must be complete and report any clinically significant laboratory abnormalities, and follow-up to the normal.

Clinical significance is defined as the researchers that have important clinical significance, require medical intervention or meet any abnormal data definition of serious adverse events ". If there are other clinical indications, clinical observation and evaluation, to determine the anomaly results significant or cause or monitoring of adverse events.

Abnormal laboratory can not explain the value, to repeat the examination, and follow-up to the value returned to normal reference range or reach the baseline, and / or find a reasonable explanation. If there is a clear explanation, please record in the case report form.

## Serious adverse events

### Definition of serious adverse event

Serious adverse events (Severe Adverse Event, SAE) refers to the following clinical events unforeseeable happen at any dose: death; life threatening; hospitalization or extend the time of hospitalization; lead to the loss of persistent or significant function, or lead to congenital malformations or birth defects.

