## Adverse events

### Definition of adverse events

Adverse events (Adverse Event AE) refers to that patients or clinical trial subjects occur adverse medical events after receiving a drug, but it is not necessarily a causal relationship with this treatment.

Significant adverse event (Significant Adverse Event) refers to the addition of serious adverse events, the occurrence of any adverse events caused by application of the corresponding medical measures (such as withdrawal of drugs, reduced dose and symptomatic treatment) and hematologic or other laboratory examination abnormality.

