### Observation, recording and reporting of adverse events/serious adverse events

Researchers should explain to subjects in detail, and ask subjects to reflect the changes of disease after treatment faithfully. Physicians should avoid suggestive question. During the test, it should pay close attention to the adverse events observed, cause analysis, judgment, and follow-up observation and recording.

For any adverse events during the trial, the occurring time, symptoms, severity, duration, treatment measures and prognosis should be recorded in the case report form and to evaluate its correlation with the experimental drugs, and the researchers do a detailed record, signing and dating.

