### Recording and report procedure of serious adverse events

During the course of clinical trials, researchers must pay close attention to the occurrence of serious adverse events. Once the occurrence of serious adverse events, should immediately stop the test, and to take the necessary measures to ensure the safety of participants, at the same time in 24 hours by phone or fax report clinical trials unit ethics committee, State Food and Drug Administration (SFDA), sponsor and Hangzhou Tigermed Co. Ltd. (CRO). Serious adverse events following main contact person:

| SFDA | Registration Division  [contact]  Safety supervision department  [contact] |
| --- | --- |
| The arbitrator: | Hangzhou Tigermed Co. Ltd.  [name]  Contact [contact]  [contact] |

Researchers must fill out a serious adverse event report within 24 hours and fax to the State Food and drug administration. The relevant medical documents shall be recorded in the original file, including laboratory and auxiliary examination results report (such as: electrocardiogram etc.).

Researchers the serious adverse events occurred trying to analyze from a clinical perspective and identified with the test drug causality.

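### The protocol limits serious adverse events to unforeseeable ones, so a foreseeable death or hospitalisation, though still recorded as an adverse event, falls outside SAE classification and 24-hour reporting

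*Protocol*

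**What the plan says.** The SAE definition in section 9.3.1 of the protocol "refers to the following clinical events unforeseeable happen at any dose". The list that follows opens with "death; life threatening; hospitalization or extend the time of hospitalization" and goes on to loss of function and congenital malformation or birth defect.

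Section 9.3.2 attaches the expedited procedure to events so defined. The investigator must "in 24 hours by phone or fax report clinical trials unit ethics committee", and must also notify the drug regulator, the sponsor and the CRO. On the written form, it says "Researchers must fill out a serious adverse event report within 24 hours".

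The general adverse event rules carry no such condition. Section 9.2.1 defines adverse events as "adverse medical events after receiving a drug, but it is not necessarily a causal relationship with this treatment". Section 9.2.2 requires: "For any adverse events during the trial, the occurring time, symptoms, severity, duration, treatment measures and prognosis should be recorded in the case report form". Section 9.2.1 also has a class of significant adverse events, which "refers to the addition of serious adverse events, the occurrence of any adverse events caused by application of the corresponding medical measures", with withdrawal of drug, dose reduction and symptomatic treatment as examples of such measures.

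**The concern.** Seriousness and expectedness are separate properties of an event. Seriousness is a matter of outcome: the patient died, was admitted, was left disabled. Expectedness is a judgement about whether the event could have been anticipated, and it is normally assessed after the event has been classed as serious. Section 9.3.1 makes the second a precondition of the first.

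Three things depend on the classification: the 24-hour telephone or fax report, the SAE form, and the SAE counts in the safety analysis of section 11.4.1. The first two cannot be repaired afterwards. An event can be reclassified at data review, but a 24-hour report that was never made stays unmade.

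The protocol itself describes problems that an investigator might call foreseeable. Section 1.1 says that hypertension often leads to heart, brain and kidney complications. Section 7.2 warns of raised serum potassium when losartan, which shares the active metabolite, is combined with certain drugs. Section 9.1.2 cites renal toxicity in animals. Participants may be exposed for 8 blinded weeks and then for 56 weeks in which everyone takes the active drug, a period whose stated purpose includes long-term safety.

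**Working it through.** No figure is involved, so the check is a reading of the sections against one another.

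**1. Scope of the qualifier.** In section 9.3.1 the word stands before the list and is attached to no single item. It therefore conditions every outcome: an event needs a listed outcome and must also be unforeseeable.

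**2. Is the word given a meaning?** Section 9.3.1 names no standard for foreseeability, no reference safety document and no list of expected events. Section 9.3.2 asks the investigator to judge causality but not expectedness. Each of the 8 centres would have to apply its own reading, so the same event could be an SAE at one centre and not at another.

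**3. Does another section cancel it?** The places where a second definition or an overriding rule might stand are these:

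| Section | What it governs | Removes the condition? |
| --- | --- | --- |
| 9.2.1 | Adverse and significant adverse events | No; does not define an SAE |
| 9.2.2 | Recording in the case report form | No; no 24-hour report |
| 9.2.3, 9.2.4 | Severity grades and causality | No; severity and causality are different scales from seriousness |
| 9.2.5, 9.3.3 | Follow-up | No |
| 9.2.6 | Laboratory abnormalities | No; refers back to the SAE definition |
| 5.2.2 | Emergency unblinding | No; cites SAEs as an example |
| 12.2 | Reporting to the ethics committee | No; names SAEs without redefining them |

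None gives an unconditional definition, and none says that foreseeable serious events are reported as well.

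**4. What happens to an event with a listed outcome that is judged foreseeable?**
- It is an adverse event under section 9.2.1, since that definition has no foreseeability condition.
- It is recorded with onset, severity, duration, treatment and outcome under section 9.2.2, and followed up under section 9.2.5.
- If it led to medical measures, it may be classed as a significant adverse event. That class appears to cover what remains apart from SAEs.
- It is not an SAE, so section 9.3.2 requires neither the form nor the 24-hour report.
- In the safety analysis of section 11.4.1 it counts among the adverse events, and possibly among the important adverse events, but not among the SAEs.

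**5. Result.** The loss is in classification, in the expedited route and in the SAE count. The event itself stays on record.

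**The case against.** The strongest objection is that this rests on one word in a rough translation. The sentence is ungrammatical. Section 9.3.1 expands SAE as severe, while the abbreviation table has serious. Translation faults occur elsewhere too: section 11.4.1 calls the main test a non-inferiority test where the synopsis calls it superiority. The source word may have meant untoward or unplanned, and nothing shows that sites worked from the English text. On the reading *unplanned in this patient*, a sudden stroke would still qualify. This stands as a limit on what can be said about intent. It does not remove the condition from the only SAE definition in the document.

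A reader might infer that foreseeable deaths and admissions would go unrecorded. The documents do not support that: sections 9.2.1, 9.2.2 and 9.2.5 require any adverse event to be recorded and followed up, and the significant-event class would catch part of what falls out of the SAE class.

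A reader might also infer a biased comparison of SAE rates between the arms. That is not shown either. Investigators are blinded in the 8-week phase, so foreseeability would be judged without knowledge of the arm. The 56-week phase has no control arm.

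Stroke in a placebo patient is a tempting illustration but a weak one. Appendix 1 puts the 10-year risk of major cardiovascular events in the medium-risk group at about 15% to 20%. Assuming a constant hazard and taking 8 weeks as 8/52 year, the 8-week risk is 1 − 0.85^(0.154/10) ≈ 0.25% to 1 − 0.80^(0.154/10) ≈ 0.34%. In 130 placebo patients that is about 0.3 to 0.4 events, even if all were medium risk. Few investigators would call such an event foreseeable in a given patient.

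**Conclusion.** The point holds as a defect in the wording of the definition. As written, section 9.3.1 excludes foreseeable events with serious outcomes from the SAE class. The SAE form and 24-hour report then do not apply to them, and they are missing from the SAE counts.

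The size of the effect cannot be calculated: the protocol gives neither an expected number of serious events nor the share that investigators would judge foreseeable. If the direction matters, the SAE count can only be too low, never too high, since the condition removes events and adds none. Sample size, power and the primary analysis are not affected.

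The conclusion assumes that the English text conveys the rule that sites apply. If the source-language definition is unconditional, the defect is confined to the translation and only the English needs correcting.

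**What to change.** Check the source-language wording of section 9.3.1. Then delete *unforeseeable*, so that any adverse event with a listed outcome, at any dose, is an SAE whether or not it was foreseeable. Add expectedness as a separate item on the SAE form, assessed after seriousness.

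The change is one word in the definition and one item on a form, and possibly brings a few more SAE reports. Sections 4.3, 5.2.2 and 9.3.2 attach other consequences to SAE status (exit, emergency unblinding, stopping). The sponsor should read them against the amended definition for consistency; no change to those rules is proposed here.

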### Recording and report procedure of serious adverse events

During the course of clinical trials, researchers must pay close attention to the occurrence of serious adverse events. Once the occurrence of serious adverse events, should immediately stop the test, and to take the necessary measures to ensure the safety of participants, at the same time in 24 hours by phone or fax report clinical trials unit ethics committee, State Food and Drug Administration (SFDA), sponsor and Hangzhou Tigermed Co. Ltd. (CRO). Serious adverse events following main contact person:

| SFDA | Registration Division  [contact]  Safety supervision department  [contact] |
| --- | --- |
| The arbitrator: | Hangzhou Tigermed Co. Ltd.  [name]  Contact [contact]  [contact] |

Researchers must fill out a serious adverse event report within 24 hours and fax to the State Food and drug administration. The relevant medical documents shall be recorded in the original file, including laboratory and auxiliary examination results report (such as: electrocardiogram etc.).

Researchers the serious adverse events occurred trying to analyze from a clinical perspective and identified with the test drug causality.

### Treatment, mode of follow-up and duration of the occurrence of serious adverse events

All serious adverse events, researchers should immediately take necessary and effective measures to solve, follow-up and returned to baseline level, proved unable to solve / permanent or death.

### Measures of subjects after pregnancy

During the study period subjects after pregnancy, must immediately stop clinical trials and told the researchers. In the treatment of study within 3 months after the end of pregnancy must also report to researchers. Researchers should put all the pregnant women with pregnancy report report to Hangzhou Tigermed Co. Ltd. in 24 hours (CRO) and sponsor. Researchers should provide the consultation, discussion on the risk of pregnancy and its influence on the fetus. Continued monitoring of patients to the end of pregnancy. The final results should be pregnancy providing research sponsor.

To participate in the study subjects were pregnant wife should also report to the researchers and the sponsor. To provide consultation and follow-up of the pregnant wife of.

# Data management

## The traceability of data, and fill in and hand over of case report form (CRF)

The most original record as the original medical records needs to save. Case report form data are derived from the original medical records, to be completed by the researchers, each selected get a random number of cases must be completed case report form. The case report form by the CRA examination, the first stock exchange statistics unit of data, data entry and management work. The first joint after the transfer case report table of contents will not be modified.

## Design and establishment of database

Establish database of clinical trials with trace management; record all the information in the CRF table. Database format will be as far as possible with the format of the CRF table corresponding to facilitate entry.

## Data encode

Not applicable.

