| **Statistical analysis** | **Estimation of sample sizes:**  This is a superior efficacy test study. The efficiency test was conducted on the main therapeutic effect index. Setting bilateral α = 0.05, *β* = 0.20, and the standard deviation SD = 7.8 mmHg, the difference of the antihypertensive effect in the two groups were detected as *D* = 3 mmHg. The distribution ratio of the patient cases in the two groups was 1:1. The estimated minimum sample size was 108 pairs. Taking into account of the factors such as dropping, the present research plan included 260 cases into the two groups with 130 cases of patients in the experiment group and the control group, respectively.  **Statistical analysis of the data set:**  Statistical analysis was conducted by using the full analysis set, per-protocol population set and safety data set. The quality control was strictly carried out in the whole process of the data statistics to ensure the authenticity of the assessment of data.  Full analysis set (Full analysis set, FAS): according to the fundamental principle of intention to treat (ITT), all the randomly enrolled subjects with more than one medication administration record and effective evaluation were included in the full analysis set. When selecting full analysis set for analysis, the latest observation LOCF (LOCF) estimation method was adopted for the estimation of the missing values. Full analysis set is the main effectiveness method for the evaluation of population in the present study.  The Per-Protocol set (PPS): PPS included all the subjects with completed prescribed treatment protocal or no serious violations of tests. The exact definition of the serious violations of the scheme will ultimately determined in the data auditing, which generally included the following situations (but they are not limited to these cases): Not meeting the inclusion criteria, having interference treatment after being selected, poor compliance, interview beyond the time window. PP set is a secondary analysis of the crowds of the effectiveness, but if the results were inconsistent with the full analysis set, detailed analysis should be done on the inconsistent results.  Safety data set (Safety Set, SS): the definition of safety data set was the subjects that at least received one time drug treatment.  **Statistical analysis method:**  Statistical analysis was conducted by using the SAS9.13 statistical analysis software for calculation. Quantitative description of the parameters included the calculation of mean, standard deviation, median, minimum value and maximum value. The description of the classified index employed the case number and percentage of the cases.  Descriptive statistics were conducted on the completion of the study. The comparison among groups was conducted on the demographic and baseline characteristics to analyze the equilibrium between groups.  Analysis of the main outcome measures: the main efficacy index will use the test of superiority. In addition, the dereasee value os DBP of each subject after treatment of 8 weeks will also be calculated, and descriptions in each group were done (mean, standard deviation, median, minimum, maximum). Comparisons between groups used analysis of variance considering center effect.  Analysis of the secondary outcome indicators: the center effect was not considered in principle. Comparisons between groups employed the variance analysis, chi-square test or nonparametric statistical method.  Analysis of the safety evaluation: parameters of safety evaluation included adverse events/ adverse drug reaction (ADR)/important adverse events or serious adverse events, physical examination and laboratory examination and a 12-lead electrocardiogram. Detailed description was conducted on the cases of adverse events during the test. The incidence rates of the adverse events between the two groups were summarized and compared. The indexes of laboratory examination were statistically described. The difference between two groups was compared when it was necessary. A detailed description of the laboratory indexes and normal cases before treatments was conducted.  This study did not conduct interim analysis. |

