**（2）Adverse reactions**

The incidence rates of the adverse reactions in the groups of Allisartan Isoproxil with 80 160, 240mg and losartan of 50mg were 8.57% (6/70), 4.35% (3/69), 9.59% (7/73) and 10% (7/70), mainly manifested as headache, dizziness, headache, nausea, abnormal liver function, of which the incidence rates of headache (4.11%) and headache (2.74%) in the group of the Allisartan Isoproxil (240mg) were the highest. The incidence rates of dizziness, abnormal liver function abd nausea in each dose group were similar. The adverse reactions mainly exhibited as mild, some were moderate, which could be alleviated themselves or alleviated after symptomatic treatments. There was no significant difference in the incidence rate of adverse reactions and severe degrees among groups.

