### Criteria of relationship between experimental drugs of adverse events/serious adverse events

Determination of the relationship between adverse events/signiciant adverse events and the test drugs:

Determination according to 5 grade criteria: that is certainly related, may be, may be independent, independent, be unable to be evaluted. The first two are adverse reactions, and the incidence rate of the adverse reaction is analyzed.

Certainly related: the appearance of reaction conforms to the reasonable time order after drug application, and the reaction conforms to the known reaction type of the suspected drugs; improvement after stopping of drug, occurrence of the reaction after repeated administration of the drug.

May be relatd: the appearance of reaction conforms to the reasonable time order after drug application, and the reaction conforms to the known reaction type of the suspected drugs; the patient's clinical status or other treatments may also induce this reaction.

Probably not related: the reaction is not in line with the reasonable time order after drug application, and the reaction is not in line with the known reaction type of the suspected; the patient's clinical status or other treatments may also induce this reaction.

Unrelated: the reaction does not comply with the time sequence after reasonable, a reaction type with non experimental drugs known reaction; the patient's clinical status or other treatments may cause the reaction, improve the state of disease or stop the elimination reaction to other treatments, the repeated use of other treatment response.

Unable to evaluate: the reaction has no relationship with the medication time, type and the drug known reaction similar to that of other drugs may also cause the same reaction.

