## Input and modification of data

Data entry and management by the Shanghai Tigermed Co. Ltd. (CRO) statistics department is responsible for, will designate special personnel data management, developing data management plan. To ensure the accuracy of the numerical data, using double entry and proofreading; adverse events and drug in combination with single input and manual check.

The present case report table in question, the data administrator will fill in question and answer form (DRQ), and send inquiries to the researchers through clinical research associate, researchers should answer as soon as possible and return the data administrator data modification according to the researcher's answer, confirmation and entry, when necessary, can be re issued DRQ.

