## Statistical methods

### Aalysis method

Statistical analysis using SAS9.13 statistical analysis software for calculation. Quantitative description of the calculation of mean and standard deviation, median, minimum value, maximum value. Classification index described by number and percentage of cases.

Completion of the study will be carried out descriptive statistics on the demographics and baseline characteristics were compared between the two groups in a balanced analysis between groups.

Analysis of the main outcome measures: the main efficacy index will adopt non inferiority test. In addition, also calculate each subject after 8 weeks of treatment, DBP decreased and the seat value groups (mean standard deviation, median, minimum and maximum), groups were compared using analysis of variance center effect considered.

Analysis of secondary efficacy indicators: in principle does not consider the center effect, by using variance analysis, chi square test or nonparametric statistical method for comparison between groups.

Analysis of safety evaluation, safety evaluation included adverse events / ADR / important adverse events or serious adverse events, physical examination and laboratory examination and a 12 lead electrocardiogram. Cases of adverse events during the detailed description of test, summary comparison of incidence of adverse events between the two groups. Statistical description and index of laboratory examination and necessary changes were compared between the two groups. A detailed description of laboratory indexes was normal before treatment after treatment of abnormal.

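### Section 10.3 rules out data coding, so adverse-event comparisons by event type would rest on ungrouped reporter terms

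*Protocol*

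**What the plan says.** Section 10.3 (Data encode) stands in the data management chapter between database design (10.2) and data entry (10.4). Its entire content is "Not applicable". The protocol names no dictionary, preferred term or grouping rule anywhere.

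Other sections plan to use adverse-event data as follows:

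- The Protocol summary, under statistical analysis, states: "The incidence rates of the adverse events between the two groups were summarized and compared".
- Section 11.4.1 repeats it: "summary comparison of incidence of adverse events between the two groups".
- Section 9.2.4 grades causality on five levels and adds: "The first two are adverse reactions, and the incidence rate of the adverse reaction is analyzed".

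On how the data arise, section 9.2.2 requires for each event that "the occurring time, symptoms, severity, duration, treatment measures and prognosis should be recorded in the case report form". Section 3 plans eight centres. Section 10.4 gives numerical data double entry but treats other items differently: "adverse events and drug in combination with single input and manual check".

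**The concern.** Section 10.3 takes a position; it does not simply leave the matter to a later document. A statistical analysis plan or data management plan that introduced coding would contradict the protocol.

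If 10.3 is followed as written, each event is tabulated under whatever words the investigator used. Two centres that describe one complaint differently then produce two rows, each with a lower rate than the event really has. A between-group comparison on either row has less power than one on the combined event.

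This matters because the trial provides the only placebo comparison in hypertensive patients that the protocol describes. The earlier phase II trial in section 1.2 compared three doses with losartan, and the placebo-controlled phase I studies there were in healthy volunteers.

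Concomitant drugs are affected in a smaller way. Section 7.2 bars several named drugs and all other antihypertensives, and interfering treatment is a ground for leaving the per-protocol set. Products are harder to recognise among uncoded names.

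**Working it through.** **1. Is there a conflict in the text?** Section 10.3 rules coding out. The Protocol summary and section 11.4.1 compare adverse-event incidence, and section 9.2.4 analyses adverse-reaction incidence. Of the safeguards nearby, section 10.4 has a manual check, queries to investigators and a data management plan. Section 10.5 has checks of range, logic, consistency and protocol deviation, and section 10.6 has blind review before lock. None of them is given the task of mapping synonyms to one term.

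**2. Which analyses depend on coding?** The proportion of subjects with at least one adverse event, adverse reaction, important event or serious event is the same however the event is worded. Rates by event type or organ class do depend on the wording. The loss is confined to those.

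**3. How large could the loss be?** The protocol gives no power figure for any adverse-event comparison, so there is nothing of its own to reproduce. The illustration uses:

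- 130 subjects per arm (Protocol summary; section 11.1);
- two-sided 0.05 for tests other than the primary (section 11.3);
- event rates and splits that are **assumptions**, not taken from the protocol.

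Let X ~ Binomial(130, p1) be the count on drug and Y ~ Binomial(130, p2) the count on placebo. Power is the sum of P(X = i) × P(Y = j) over all pairs (i, j) for which the two-sided Fisher exact p-value is at most 0.05. An even split over k terms divides both rates by k. An 80/20 split multiplies them by 0.8 for the larger term.

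| Assumed true rates | How reported | Rates per term | Fisher power per term |
|---|---|---|---|
| 8% vs 1% | one grouped term | 8% vs 1% | 0.733 |
| 8% vs 1% | two terms, even | 4% vs 0.5% | 0.274 |
| 8% vs 1% | three terms, even | 2.67% vs 0.33% | 0.094 |
| 8% vs 1% | two terms, 80/20 (larger) | 6.4% vs 0.8% | 0.589 |
| 10% vs 2% | one term; two even | 10% vs 2%; 5% vs 1% | 0.723; 0.319 |
| 15% vs 5% | one term; two even | 15% vs 5%; 7.5% vs 2.5% | 0.720; 0.338 |
| 5% vs 1% | one grouped term | 5% vs 1% | 0.32 |
| 4% vs 1% | one grouped term | 4% vs 1% | 0.18 |

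**4. Detection on any of the split terms.** Per-term power overstates the loss, because a signal on either term would be noticed. Treating the terms as roughly independent, for 8% vs 1%:

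- two even terms: 1 − (1 − 0.274)² = 0.47;
- three even terms: 1 − (1 − 0.094)³ = 0.26.

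Both are below the 0.73 for the grouped event.

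**5. A worked count.** Suppose 13 subjects on drug and 3 on placebo have the event. Grouped, 13/130 against 3/130 gives Fisher p = 0.018. Split as 7 against 2 and 6 against 1, the p-values are 0.17 and 0.12.

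**The case against.** **The planned comparison may not be by term.** Neither the Protocol summary nor section 11.4.1 says that incidence is compared by event type, and the overall rates do not need a dictionary. This stands, and it limits the point to tabulations by event type. These are likely, since the earlier phase II results in section 1.2 are described partly by named event, but the protocol does not spell them out.

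**The figures depend on the scenario.** This also stands. The rates are assumed and an even split is unfavourable: under an 80/20 split the larger term keeps 59%. Coding does not rescue smaller differences, since 5% against 1% has only 32% power when fully grouped. The protocol powers no adverse-event test.

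**The heading is a translation.** Elsewhere encoding refers to randomisation or drug numbers (section 5.2.2). But that activity does apply in this trial, so it is hardly what 10.3 declares inapplicable. Given its place in the data management chapter, coding of reported data is the natural reading, though not a certain one.

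**Other checks may help.** Named prohibited drugs, queries, manual checks and blind review reduce the concomitant-drug problem. They do not replace grouping of event terms.

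A reader might infer more from two places, and the document does not support either inference. First, section 1.2 reports for the earlier trial "the incidence rates of headache (4.11%) and headache (2.74%) in the group of the Allisartan Isoproxil (240mg) were the highest", which can look like one event split in two. An uncoded table would merge identical words, so two rates more probably reflect two source-language terms translated alike. Nothing says whether that trial was coded or whether the two are one event. The repetition is not evidence of splitting. Second, this might be taken for the first placebo-controlled trial of the drug. Section 1.2 describes placebo-controlled single-dose and multiple-dose studies in healthy subjects, so only the narrower statement about hypertensive patients holds.

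**Conclusion.** The point holds in a limited form. Section 10.3 rules out coding while other sections plan incidence summaries and comparisons from investigator-recorded entries at eight centres, and nothing else in the protocol groups synonymous terms. Overall adverse-event and adverse-reaction rates are sound. Tables or comparisons by event type would be fragmented, with understated rates and less chance of seeing a difference from placebo.

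The size cannot be fixed from the document. Under the assumed 8% against 1%, detection falls from 73% to about 47% on either of two evenly split terms; a less even split costs less. These figures assume that synonyms actually occur, that the stated splits hold, and that the terms are roughly independent. They show that a real difference could be missed, not that one would be. Severity is low.

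**What to change.** Replace the entry in section 10.3 with a statement along these lines: adverse events are coded to a standard medical dictionary (term and organ class) and concomitant drugs to a standard drug dictionary; the dictionary versions are recorded; coding is done by staff blind to group and is completed before blind review and database lock. In section 11.4.1 and the Protocol summary, add that incidence is counted as subjects per coded term and per organ class, alongside the overall rates.

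The cost is dictionary use and some coder time before lock. No new patient data are needed, and no clinical rule changes.
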